## Abstract

**Background:**

Previous research has suggested an association between more liberal red blood cell (RBC) transfusion and greater risk of further bleeding and mortality following acute upper gastrointestinal bleeding (AUGIB).

**Methods and design:**

The Transfusion in Gastrointestinal Bleeding (TRIGGER) trial is a pragmatic cluster-randomised feasibility trial which aims to evaluate the feasibility of implementing a restrictive *vs.* liberal RBC transfusion policy for adult patients admitted to hospital with AUGIB in the UK. This trial will help to inform the design and methodology of a phase III trial. The protocol for TRIGGER has been published in Transfusion Medicine Reviews. Recruitment began in September 2012 and was completed in March 2013. This update presents the statistical analysis plan, detailing how analysis of the TRIGGER trial will be performed. It is hoped that prospective publication of the full statistical analysis plan will increase transparency and give readers a clear overview of how TRIGGER will be analysed.

**Trial registration:**

ISRCTN85757829

## Update

### Introduction

Acute Upper Gastrointestinal Bleeding (AUGIB) is the most common reason for emergency hospital admission with a gastrointestinal disorder in the United Kingdom (UK) with an annual incidence of 50 to 150/100,000 adults [1]. It is also the leading indication for red blood cell (RBC) transfusion, accounting for 14% of all RBCs transfused in England [2]. RBC transfusion is commonly based upon the patient’s haemoglobin (Hb) level; however, the optimal Hb threshold at which to transfuse is unclear [3,4]. Two observational studies have indicated an association between RBC transfusion after AUGIB and risk of further bleeding and mortality [5,6]. A recently published randomised trial found a liberal approach to transfusion led to an increased risk of mortality [7], although these results may not be generalisable due to the strict protocols of care implemented in this single centre trial, which are unlikely to be reproducible in most healthcare institutions.

The Transfusion in Gastrointestinal Bleeding (TRIGGER) trial is a cluster-randomised trial designed to evaluate the feasibility of implementing a restrictive *vs.* liberal RBC transfusion policy for patients admitted to hospital with AUGIB [8]. TRIGGER is a pragmatic trial which aims to reflect real world settings as closely as possible. Six hospitals in the United Kingdom were randomised in a 1:1 ratio to follow either a liberal transfusion policy (where eligible patients are transfused when their Hb drops below 10 g/dL) or a restrictive transfusion policy (where eligible patients are transfused when their Hb drops below 8 g/dL). Randomisation was performed using permuted blocks without stratification or matching, with a block size of six (to ensure three hospitals in each arm). Hospitals were randomised in July 2012, and recruitment took place between September 2012 and March 2013.

The TRIGGER protocol has been published in Transfusion Medicine Reviews [8] (available at http://www.tmreviews.com), and gives details on the rationale for the study, the inclusion/exclusion criteria, the sample size calculation and the process for consenting patients to the trial. This update to the published protocol describes the statistical analysis plan for TRIGGER.

The TRIGGER trial was conducted according to the declaration of Helsinki, and received ethical approval from the Scotland A Research Ethics Committee (Reference 12/SS/0023) and the NRES Committee South Central – Oxford C (Reference 12/SC/0062).

### Outcomes

This trial will report both feasibility and clinical outcomes. Outcome definitions and explanations are available in the protocol [8].

### Feasibility outcomes

The feasibility outcomes are:

• The proportion of eligible patients who provide consent

• The proportion of screened patients who are ineligible due to need for immediate transfusion

• Overall protocol adherence

• Protocol adherence per patient

• Protocol adherence per Hb count

• Baseline characteristics of consented patients (age, shock, Hb, clinical Rockall score [9], Blatchford score [10] (two commonly used risk scores), and number of major co-morbidities for consented patients)

• The difference between consented vs non-consented patients for baseline Hb, Rockall and Blatchford scores

• The number of RBC units transfused

• The proportion of patients receiving at least one RBC transfusion

• Mean Hb over the first seven days, up to discharge, and over the entire study period

• Differences between consented patients and those discharged before being approached for consent in the Rockall and Blatchford scores, and baseline Hb.

The intra-class correlation coefficient and its 95% confidence interval from this feasibility trial will also be presented.

### Clinical outcomes

The clinical outcomes are:

• Further bleeding up to Day 28 (primary clinical outcome)

• Further bleeding up to hospital discharge

• All-cause mortality up to Day 28

• All-cause mortality up to hospital discharge

• Therapeutic intervention at the index endoscopy

• Surgical or radiological intervention to control bleeding up to death or discharge

• Occurrence of a thromboembolic or ischaemic event up to Day 28

• Occurrence of a thromboembolic or ischaemic event up to hospital discharge

• Acute transfusion reactions up to death or discharge

• Infection up to Day 28

• Infection up to hospital discharge

• Length of hospital stay

• Health related quality of life at Day 28

• Serious adverse events (SAEs) up to Day 28

The individual components that make up the composite outcome of a thromboembolic or ischaemic event (myocardial infarction, stroke, pulmonary embolus, deep vein thrombosis, and acute kidney injury) will also be analysed separately at both Day 28 and at hospital discharge.

## Analysis principles

### Feasibility outcomes

Analysis of the feasibility outcomes will be by intention-to-treat (ITT), and will include all consented patients on whom an outcome is available, unless otherwise stated. A secondary analysis will include all consented patients with a recorded Hb below 12 g/dL during follow-up, and for whom an outcome is available (this secondary analysis will be restricted to RBC transfusion outcomes, Hb concentration outcomes, and adherence outcomes). A 5% significance level will be used. All analyses of feasibility outcomes will be unadjusted for baseline covariates.

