### Adjusted analyses

Adjusted analyses using cluster-level summaries will be performed as follows [14]:

1) A regression model (linear for continuous outcomes and logistic for binary outcomes) will be fit to individual-level patient data, and will be adjusted for the baseline characteristics listed earlier (age, shock, presence of coagulopathy and the number of major co-morbidities). The model will not adjust for treatment effect, or for centre.

2) Predicted values based on the fitted regression model will be calculated for each patient (for binary outcomes this equates to the predicted probability of experiencing an event, for continuous outcomes this equates to the predicted mean).

3) The expected outcome in each cluster will be calculated. For binary outcomes, this is the expected number of events in each cluster, and is calculated by summing the predicted probabilities for each patient in that cluster. For continuous outcomes, the expected mean value is calculated by taking the mean of the predicted values in each cluster.

4) An appropriate residual is calculated for each cluster. For binary outcomes, this is the observed number of events minus the expected number of events, divided by the number of patients in the cluster. For continuous outcomes, this is the observed mean minus the expected mean.

5) A linear regression model will be fit using the residuals calculated above as cluster-level summaries, with only the treatment group as a covariate. No degrees of freedom correction will be made for performing an adjusted analysis, as only patient-level variables will be adjusted for.

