### Cluster level summaries for feasibility outcomes

Cluster-level summaries for feasibility outcomes will be calculated separately in each centre as follows:

1) **Recruitment rate (patients consenting):** the proportion of eligible patients providing consent.

2) **Ineligible due to severity of bleeding:** the proportion of screened patients who are ineligible due to severity of bleeding

3) **Overall adherence:** the mean adherence rate per patient

4) **Adherence per patient:** the proportion of patients who had no protocol deviations

5) **Adherence per Hb count:** the proportion of Hb counts that did not lead to a protocol deviation

6) **Selection bias - baseline variables for consented patients:** The mean age, baseline Hb, number of major co-morbidities, clinical Rockall score and Blatchford score, and the proportion of patients with shock will be calculated for consented patients.

7) **Selection bias - difference between consented and non-consented patients in baseline variables:** The difference in the mean Rockall score and Blatchford score, and mean baseline Hb between consented and non-consented patients will be calculated in each centre.

8) **Red blood cell exposure (number of transfusions):** the mean number of RBC units transfused per patient.

9) **Red blood cell exposure (patients receiving at least one transfusion):** the proportion of patients who receive at least one RBC transfusion.

10) **Hb concentration up to Day 7, and over the entire in-hospital follow-up period, prior to discharge/death/Day28:** the area-under-the-curve will be calculated for each patient

11) **Hb concentration at discharge:** the mean Hb will be calculated

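### The Hb and RBC-use feasibility outcomes get no analysis adjusted for baseline Hb, although it is recorded and the SAP already contains a suitable method

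*SAP article*

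**What the plan says.** Under Analysis principles, Feasibility outcomes, the SAP article sets one rule for main and secondary analyses alike: "All analyses of feasibility outcomes will be unadjusted for baseline covariates". The same paragraph adds "A 5% significance level will be used". No reason is given for excluding adjustment.

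The list under Outcomes, Feasibility outcomes shows what the rule covers. It includes "The number of RBC units transfused", the proportion of patients with at least one RBC transfusion, and "Mean Hb over the first seven days, up to discharge, and over the entire study period". It also includes "Baseline characteristics of consented patients (age, shock, Hb, clinical Rockall score" and further items, so baseline Hb is recorded. Cluster level summaries for feasibility outcomes summarises it by centre ("The mean age, baseline Hb, number of major co-morbidities, clinical Rockall score and Blatchford score") and, in an item labelled as selection bias, contrasts it by consent status: "The difference in the mean Rockall score and Blatchford score, and mean baseline Hb between consented and non-consented patients".

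The Adjusted analyses section sets out a two-stage method for cluster-level summaries, beginning "A regression model (linear for continuous outcomes and logistic for binary outcomes) will be fit to individual-level patient data". It makes no degrees-of-freedom correction, because only patient-level variables enter. That method serves the secondary analyses of the clinical outcomes, which adjust for age, shock, co-morbidities and coagulopathy, but not baseline Hb.

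**The concern.** Baseline Hb is the pre-policy value of the Hb outcomes. Both policies act on Hb thresholds (Introduction), so it should also predict RBC use. Leaving it out has two possible costs.

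- **Precision.** Six hospitals were randomised three to three without stratification or matching. The comparison rests on six points and 4 residual degrees of freedom. Any between-hospital variation in baseline Hb adds to the noise in the Hb and RBC contrasts.
- **Bias, under a condition.** Hospitals were randomised in July 2012 and recruitment began in September 2012, so patients entered after their hospital's policy was set. If the recruited patients differ by arm in baseline Hb, part of that difference appears as a policy effect. The plan will describe such an imbalance, but has no estimate that allows for it.

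At stake is how clearly a feasibility trial meant to inform a phase III design can show whether the two policies led to different Hb levels and RBC use.

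**Working it through.** The article states no variance or power figure for these outcomes, so there is nothing to reproduce.

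**From the SAP article:** six hospitals, 3 v 3; equal cluster weights; linear regression on cluster summaries (4 df, two-sided critical t 2.776, two-sidedness being assumed); two-stage residual method.

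**Assumed:** m = 100 patients per hospital; SD of baseline Hb 3 g/dL; SD of mean follow-up Hb 1.5 g/dL (2 as an alternative); patient-level correlation ρ 0.3 to 0.7; baseline ICC 0 to 0.05; residual outcome ICC 0.01 to 0.05; the same baseline slope between hospitals as within them.

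**Step 1: chance imbalance in baseline Hb.** Write V(ICC) = ICC + (1 − ICC)/m, so V(0) = 0.0100, V(0.01) = 0.0199 and V(0.05) = 0.0595. The SD of the arm difference is 3 × √V × √(2/3): 0.24, 0.35 and 0.60 g/dL respectively.

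**Step 2: carry-over.** Slope = ρ × SD(outcome)/SD(baseline). Carry-over = slope × imbalance, here 0.5 g/dL.
- Outcome SD 1.5: slopes 0.15, 0.25, 0.35 at ρ = 0.3, 0.5, 0.7; carry-over 0.075, 0.125, 0.175 g/dL.
- Outcome SD 2: slopes 0.20, 0.33, 0.47; carry-over 0.10, 0.17, 0.23 g/dL.

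**Step 3: precision for mean Hb.** With the stage-1 slope well estimated, the ratio of adjusted to unadjusted variance is

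(1 − ρ²)V(ICC_res) / [ρ²V(ICC_base) + (1 − ρ²)V(ICC_res)].

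Simulation of the SAP's two methods (3,000 trials per setting, outcome SD 1.5, true difference 0.5 g/dL) agrees:

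| ρ | Baseline ICC | Residual ICC | Ratio, formula | Ratio, simulated | Power, unadjusted to adjusted |
|---|---|---|---|---|---|
| 0.3 | 0 | 0.05 | 0.98 | 0.98 | 0.25 to 0.26 |
| 0.5 | 0.01 | 0.05 | 0.90 | 0.90 | 0.28 to 0.30 |
| 0.5 | 0.01 | 0.01 | 0.75 | 0.75 | 0.60 to 0.71 |
| 0.7 | 0.05 | 0.05 | 0.51 | 0.50 | 0.26 to 0.44 |
| 0.7 | 0.05 | 0.01 | 0.26 | 0.26 | 0.35 to 0.86 |

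Across all simulated settings the variance fell by 2% to 75%.

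**Step 4: validity.** With no policy effect and no systematic imbalance, rejection rates were 0.043 to 0.058 unadjusted and 0.041 to 0.059 adjusted. With a systematic 0.5 g/dL baseline shift and no policy effect, the unadjusted difference averaged about 0.08, 0.13 and 0.17 g/dL at ρ = 0.3, 0.5 and 0.7, and 5% to 14% of trials rejected. After adjustment the mean was about 0 and rejection 4% to 6%.

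**Step 5: any RBC transfusion.** A smaller simulation used the logistic first stage: 1,000 trials per setting, 100 patients per centre, baseline SD 3, baseline ICC 0.01 to 0.05, log-odds slope −0.3 or −0.6 per g/dL, between-centre log-odds SD 0.2 or 0.4. Adjusted variance was 0.34 to 0.91 of unadjusted. A 0.5 g/dL baseline shift with no policy effect gave spurious differences of about 3 to 5 percentage points, and about 0 after adjustment. RBC unit counts were not simulated.

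**The case against.** The unadjusted comparison of cluster summaries is a legitimate analysis of a 3 v 3 trial. The rule is clear, and it matches the clinical outcomes, whose main analyses are also unadjusted. A reader might infer that baseline imbalance makes the feasibility results invalid or that the SAP contradicts itself. The document supports neither. Chance imbalance between hospitals is already reflected in the between-cluster variance and the 4-df interval, and Step 4 shows that type I error holds. Bias needs differential recruitment after allocation. The article recognises that risk and gives no evidence that it occurred.

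The gain may also be small. With outcome SD 2, ρ = 0.5, outcome ICC 0.05 and baseline ICC 0 to 0.02, a separate simulation of 4,000 trials gave a confidence-interval half-width of about 1.03 g/dL unadjusted against 0.96 to 1.01 adjusted. Power went from 16–17% to 16–19%. If local transfusion practice drives the differences between hospitals, baseline Hb explains little of them. The larger gains need baseline Hb to explain differences between hospitals as strongly as differences between patients.

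Finally, the policies are threshold rules, so the relation of RBC use to baseline Hb may be non-linear and may differ by arm.

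All of this stands, and it limits the size of the point and the remedy. It does not remove the point: describing baseline Hb by arm supplies no adjusted estimate, and a valid test does not recover lost precision.

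**Conclusion.** The point holds as a nearly free improvement, not as an error. No analysis of the Hb or RBC-use outcomes allows for baseline Hb, although the data and the method are both in the plan.

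The size cannot be fixed from the article. Under the assumed ranges the variance of the mean-Hb difference falls by about 2% to 75%. A 0.5 g/dL recruitment imbalance would bias the unadjusted mean-Hb difference by about 0.08 to 0.23 g/dL. Adjustment would remove only the part due to baseline Hb, not other differences between the patients recruited in each arm.

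A reader might also conclude that the adjusted result should replace the unadjusted one as the main analysis. The document does not support that. Its own hierarchy for clinical outcomes puts unadjusted first and adjusted second, and the gain here depends on unknown inputs.

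**What to change.** In Analysis principles, Feasibility outcomes, keep the unadjusted analysis and qualify the blanket rule. For RBC units, any RBC transfusion and the Hb outcomes, prespecify an additional analysis by the method under Adjusted analyses, as follows:

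- Use patient-level baseline Hb as the stage-1 covariate, with a linear first stage for units and Hb and a logistic one for any transfusion.
- Give baseline Hb a flexible form, for example the fractional polynomials already planned for age and co-morbidities.
- State that missing baseline Hb is handled by the within-centre mean imputation already planned for the clinical covariates.
- Report the adjusted result beside the unadjusted one.

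Leave the consent, eligibility and baseline-comparison outcomes unadjusted, since adjustment has no purpose there.

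The cost is a few sentences in the SAP and a little analysis work. No new data are needed. No degrees of freedom are lost, because baseline Hb enters as a patient-level variable.

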### Clinical outcomes

Main analysis of the clinical outcomes will be by ITT, and will include all consented patients with a recorded Hb below 12 g/dL during follow-up, and for whom the outcome is available. Including only patients with a Hb <12 g/dL allows us to target those patients most likely to be affected by the treatment policy, resulting in a more powerful analysis on a more relevant patient population. A Hb of 12 g/dL was chosen as the cut-off point because it is likely that some patients will be transfused (against policy) above 10 g/dL; if the proportion of patients transfused above 10 g/dL differs between treatment arms, excluding these patients could lead to bias. Using a cut-off of 12 g/dL should allow the majority of transfused patients to be included in the analysis, leading to an unbiased comparison. A secondary analysis will include all consented patients, regardless of whether their Hb dropped below 12 g/dL.

Results will be considered statistically significant at the 5% level. Main analyses for clinical outcomes will be unadjusted for baseline covariates; however, a set of secondary analyses will be adjusted for patient age, the presence of shock, the number of major co-morbidities, and the presence of coagulopathy (defined as an international normalised ratio (INR) >1.5 or a prothrombin time (PT) >3 seconds greater than the control). Mean imputation within the centre will be used for patients with missing baseline covariates [11]. Patient age and the number of major co-morbidities (encompassing ischaemic heart disease, cardiac failure, liver disease, renal disease, respiratory disease, malignancy and stroke) will be modelled using fractional polynomials to allow for the possibility of a non-linear association [12]. Further bleeding up to Day 28 is regarded as the primary clinical outcome.

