### Analysis methods

All analyses will account for clustering to ensure correct type I error rates and confidence intervals [13-15]. Many cluster randomised trials base their analysis on individual level patient data, and use appropriate statistical methods to account for clustering between patients in the same cluster (for example, mixed-effects models or generalised estimating equations). However, analysis methods based on individual level patient data may not perform well when the number of clusters is small [13,14]. Analysis for TRIGGER will, therefore, be performed using cluster-level summaries, which performs well even with a very small number of clusters [13,14].

Equal weight will be given to each of the six clusters. All analyses will compare the two treatment arms, unless otherwise stated. Binary outcomes will be presented as a difference in proportions.

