### Cluster level summaries for clinical outcomes

The cluster-level summary will be calculated as the proportion of patients in each centre experiencing the event of interest for the following outcomes: further bleeding, all-cause mortality, need for therapeutic intervention at index endoscopy, need for surgery or radiological intervention to control bleeding, any thromboembolic or ischaemic events (and each of the components separately), acute transfusion reactions, infections and SAEs.

A cluster-level summary for length of hospital stay will be calculated using the median length of stay in each centre, and a cluster-level summary for health related quality of life will be calculated using the mean EQ-5D [16] in each centre.

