### Sensitivity analyses

Missing data for each clinical outcome will be summarised by treatment arm. Sensitivity to missing data for further bleeding and all-cause mortality up to Day 28 will be assessed under a range of missing-not-at-random scenarios. This will be done by calculating the mean outcome in each cluster as follows:

$$\left(x_{\mathrm{obs}}\right)\left(1-p_{\mathrm{missing}}\right)+\left(x_{\mathrm{sensitivity}}\right)\left(p_{\mathrm{missing}}\right)$$

where *x*_*obs*_ is the observed cluster level summary, *p*_*missing*_ is the proportion of patients with missing data in that cluster, and *x*_*sensitivity*_ is the proportion of patients with missing data who are assumed to have had the event of interest. *x*_*sensitivity*_ will be varied between 0, 0.2, 0.4, 0.6, 0.8 and 1. The treatment effect and 95% confidence interval will be calculated as before.

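### If patients are lost after discharge, the main analysis of binary Day 28 outcomes probably keeps in-hospital events but drops event-free patients, overstating event rates by an amount that depends on each hospital's loss

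*SAP article*

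**What the plan says.** Under Analysis principles, Clinical outcomes, the main analysis "will include all consented patients with a recorded Hb below 12 g/dL during follow-up, and for whom the outcome is available". Under Cluster level summaries for clinical outcomes, "The cluster-level summary will be calculated as the proportion of patients in each centre experiencing the event of interest"; no censoring or other use of partial follow-up is described. Analysis methods adds: "Equal weight will be given to each of the six clusters".

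The list of clinical outcomes includes "Further bleeding up to Day 28 (primary clinical outcome") and, separately, "Further bleeding up to hospital discharge". Mortality, thromboembolic or ischaemic events (with their components) and infection also appear at both horizons. SAEs are listed to Day 28 only.

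The Sensitivity analyses section states: "Sensitivity to missing data for further bleeding and all-cause mortality up to Day 28 will be assessed under a range of missing-not-at-random scenarios". The missing share in its formula "is the proportion of patients with missing data in that cluster", and the assumed event share among missing patients takes the values 0, 0.2, 0.4, 0.6, 0.8 and 1. Missing data are summarised by arm for every clinical outcome.

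**The concern.** For a yes/no outcome accumulated to Day 28, whether the answer is known depends on what the answer is. A death or rebleed in hospital fixes it, whatever follow-up comes later. A patient seen to be event-free until discharge and then unreachable has no Day 28 answer. If that patient leaves the denominator while the early event stays in the numerator, the hospital's proportion is too high, and more so the more patients it loses.

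Two things are at stake. One is the level of the event rates, which a feasibility trial passes on to the design of the phase III trial. The other is the comparison of policies: with three equally weighted hospitals per arm, one poorly followed hospital moves its arm mean by a third of its own bias. The plan uses the same reasoning itself when it defends the 12 g/dL cut-off on the ground that exclusions differing between arms could bias the comparison.

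**Working it through.** The article gives no event rate and no loss rate, so there is no stated figure to reproduce. The inputs below are assumptions.

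**Inputs.** In-hospital risk a = 0.08; post-discharge risk to Day 28 as a share of all patients b = 0.02; true rate a + b = 10%. L is the fraction lost among patients event-free at discharge, with loss unrelated to later events. In-hospital events always count as available.

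**Formulas.**
- Missing share: m = (1 − a) × L
- Available-case rate: [a + b(1 − L)] / (1 − m)
- Planned sensitivity value at assumed event share x: (available-case rate) × (1 − m) + x × m

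| L | m | Available-case rate | x = 0 | x = 0.2 |
|---|---|---|---|---|
| 10% | 0.092 | 0.098 / 0.908 = 10.8% | 9.8% | 11.6% |
| 20% | 0.184 | 0.096 / 0.816 = 11.8% | 9.6% | 13.3% |
| 30% | 0.276 | 0.094 / 0.724 = 13.0% | 9.4% | 14.9% |

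**When the bias vanishes.** If lost patients have later risk r, the bias equals m × (available-case rate − r). At L = 30% it is zero only if r = 13.0%. Among patients event-free at discharge the assumed later risk is 0.02 / 0.92 = 2.2%, which gives 0.276 × (0.130 − 0.022) = 3.0 points. If r exceeds 13.0%, the rate is understated.

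**Effect on the comparison, no true difference.** Equal loss gives 0. Loss of 10% in one arm and 30% in the other gives 12.98 − 10.79 = 2.2 points. If only one of three hospitals in an arm has 30% loss and all others 10%, the shift is 2.2 / 3 = 0.7 points.

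**Effect with a true difference and equal loss.** Take in-hospital risks of 12% and 8%, a 3% later risk in those event-free at discharge, and 20% loss in both arms. The true difference is 0.04 × 0.97 = 3.88 points. The available-case rates are 0.14112 / 0.824 = 17.13% and 0.10208 / 0.816 = 12.51%, a difference of 4.62.

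**What the planned grid shows at 10% v 30% loss.** The difference between arms is 9.4 − 9.8 = −0.4 points at x = 0, 14.92 − 11.64 = +3.3 at 0.2, +7.0 at 0.4 and +18.0 at 1. The truth, zero, lies between the first two values. The grid has nothing between them, although a low post-discharge risk, such as the assumed 2.2%, falls there.

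**Using the partial follow-up.** Let p1 be the proportion with the event by discharge and p2 the proportion with a later event among those event-free at discharge and followed. Then p1 + (1 − p1) × p2 = 0.08 + 0.92 × (0.02 / 0.92) = 10.0% at every L. In a simulation with varying lengths of stay and random loss at discharge (true rate 9.9%), this summary gave 9.9% at each loss level. Kaplan-Meier gave 10.3% at 10% loss and 11.0% at 30%: patients lost at discharge are censored while those still in hospital, at higher hazard, remain in the risk set.

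**The case against.** The strongest reply is that the keep-and-drop rule is inferred. The article does not say how either kind of partly followed patient is classed, and it refers outcome definitions to the protocol, which is not at hand. If patients with an event were dropped at the same rate as the others, there would be no bias. This stands as a limit on certainty. But that reading would discard known primary events, which fits poorly with a rule that includes all patients whose outcome is available.

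Second, loss may be small, and a difference as large as 10% v 30% between arms has no support in the document. That also stands.

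Third, the sensitivity analysis already puts lost patients back at each hospital's own missing share, and an available-case main analysis backed by such an analysis is conventional in a feasibility trial. This is largely right for further bleeding and mortality. It leaves the main estimate as it is, and it covers no other Day 28 outcome.

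A reader might go further and infer that the primary estimate is biased, or that the trial will show a false policy effect. The documents do not support either. The first needs material loss and a later risk in lost patients below the observed rate; the second, when the policies truly do not differ, also needs unequal loss between the arms. Nor would a time-to-event curve fully cure the problem, as the simulation shows.

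**Conclusion.** The point holds conditionally. If patients are lost after discharge, and 'available' has its natural meaning, the main analysis overstates a hospital's Day 28 event rate unless lost patients' later risk is as high as the observed rate. Under the assumed 8% and 2% risks, the excess is 0.8 points at 10% loss and 3.0 points at 30%. The arm comparison is affected mainly through unequal loss: 2.2 points at 10% v 30%, nothing at equal loss when there is no true difference, and a modest exaggeration of a true one.

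For further bleeding and mortality, the planned scenario with no events among missing patients nearly removes the excess, but only outside the main analysis. Thromboembolic or ischaemic events and their components, infection and SAEs have no such check. The change is worth making because a better summary is available from outcomes the plan already defines.

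**What to change.** 1. State how partly followed patients are classed for each binary Day 28 outcome.

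2. For the Day 28 outcomes also recorded to discharge (further bleeding, mortality, thromboembolic or ischaemic events and components, infection), keep every patient in the analysis set with known discharge status. Use p1 + (1 − p1) × p2 as the hospital's summary, where p1 is the proportion with the event by discharge (or by Day 28, if still in hospital) and p2 is the proportion with a post-discharge event by Day 28 among those discharged alive, event-free and followed. For non-fatal outcomes, a patient who dies in hospital before the event counts as event-free and has no post-discharge period, so such deaths come out of the multiplier of p2, as do event-free patients still in hospital at Day 28. Enter the six values in the same regression. A per-hospital cumulative incidence curve is an alternative, but it reduces the bias rather than removing it.

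3. In the sensitivity analysis, define the assumed event share as the post-discharge risk of lost patients known to be event-free at discharge, add values between 0 and 0.2, and extend the analysis to the other binary Day 28 outcomes, including SAEs.

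The cost is wording and modest programming. No event dates are needed: an event by Day 28 but not by discharge is a post-discharge event. There are two downsides. The p2 term assumes that loss after event-free discharge is non-informative. The observed-minus-expected step in Adjusted analyses and the proportions in Subgroup analyses need matching handling, so that all analyses treat loss alike.
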